## Abstract

**Background:**

Self-harm is a major health concern amongst young people that is increasing in prevalence. Cognitive analytic therapy (CAT) is a relational, integrative psychotherapy that is theoretically consistent with our growing understanding of self-harm. The aim of this study was to ascertain the feasibility and acceptability of evaluating brief CAT in young people aged 13–17 who self-harm using a randomised controlled trial (RCT) design.

**Method:**

Sixty young people with experiences of self-harm will be recruited from child and adolescent mental health services. Participants will be randomly allocated (1:1 ratio) to brief CAT plus treatment as usual (TAU) or TAU alone. Assessors will be blind to treatment allocation. Assessments will occur at baseline, 8, 16, and 20 weeks after randomisation. A qualitative process evaluation will investigate experiences of the therapy and trial procedures. The primary outcome for this study is feasibility, judged against a priori progression criteria relating to recruitment, retention, adherence to therapy, and missing data.

**Discussion:**

Brief CAT may help young people struggling with self-harm, but research is needed. In order to undertake a definitive RCT, it is first necessary to resolve a number of feasibility uncertainties. The planned feasibility trial will help inform a larger definitive trial focused on the efficacy of brief CAT for young people who self-harm.

**Trial registration:**

The trial was pre-registered (01/08/25) on ISR CTN (ISRCTN code: ISRCTN11505839).

**Supplementary Information:**

The online version contains supplementary material available at https://doi.org/10.1186/s40814-026-01880-0.

## Introduction

Self-harm, encompassing acts of self-injury and overdose irrespective of suicidal intent [1], often starts during adolescence with self-harm amongst young people increasing in recent years [2–6]. A meta-analysis of global self-harm rates in children and adolescents suggests a lifetime prevalence of 14% [7]. The occurrence of self-harm behaviour is associated with an increased risk of future self-harm and suicide, as well as physical and mental health difficulties [8–11]. Whilst there is evidence that psychological approaches can help young people who self-harm, this evidence remains scarce [12, 13]. Effective intervention with young people who self-harm may prevent further occurrence and escalation of these difficulties. Given the growing pressures facing child and adolescent mental health services (CAMHS; [14]), brief intervention holds the promise of filling gaps in service provision and enabling more rapid access to therapy.

One potential brief therapy that could be helpful for young people who self-harm is brief cognitive analytic therapy (CAT). Cognitive analytic therapy (CAT; [15]) is a time-limited, relational therapy, which has already been investigated as an approach for young people with complex difficulties [16–18]. brief CAT has been developed as an 8-session approach and already investigated in adults who self-harm [19]. However, there are currently no trials of brief CAT for young people who self-harm. CAT is usually 16 or 24 sessions long. The 8-session format of brief CAT was guided by the recognised value of shorter interventions in reducing waiting times and the additional benefit to young people in fitting around education and other commitments.

CAT focuses on identifying unhelpful relational patterns that underlie presenting difficulties. The therapist then helps the client to better recognise these patterns and find alternative, more adaptive ways of being and responding [15]. Interpersonal processes and context play an important role in self-harm [20]. Qualitative research also suggests that self-acceptance and forging more positive relationships with others aid recovery from self-harm [21, 22]. CAT is able to work with these relational processes and so may be well suited to helping people who self-harm. A recent meta-analysis of 25 studies provides support for CAT but studies to date predominantly focussed on adults [23]. Case series of brief CAT-informed approaches in young people (13–17 years) or are in eating disorder services (15–24 years) support the acceptability of this approach [16, 18], with positive feedback and good attendance rates. A randomised controlled trial (RCT) in young people [15–18] meeting criteria for sub-clinical or full borderline personality disorder comparing CAT to good standard care reported a faster reduction in internalising and externalising symptoms in the CAT arm [17].

National guidelines currently recommend cognitive behavioural therapy (CBT) and, where emotion-regulation difficulties are present, dialectical behaviour therapy (DBT) as treatments [1]. Whilst there is support for these approaches, it remains limited [12, 13]. For example, a meta-analysis reported small treatment effects and noted effects across therapies were smaller in young people [13]. DBT is an intensive approach involving multiple components including groups, parental involvement, one-to-one therapy, and telephone coaching. Such intensive interventions may not always be suitable or necessary for all young people and so alternatives are needed [24]. Both CBT and DBT have a largely behavioural focus. CAT, as a relational therapy, if found to be effective, may provide a valuable alternative that enhances patient choice. Consequently, brief CAT for self-harm warrants further investigation, and if found to be effective would help improve the range of treatment options in services.

Prior to evaluating the efficacy of brief CAT for young people who self-harm, it is important to determine the feasibility of investigating this approach within an RCT design. A feasibility trial can help answer important feasibility uncertainties and identify barriers and challenges that can help inform the design of a larger efficacy trial [25]. A recent feasibility trial has supported the feasibility and acceptability of brief CAT for adults who self-harm [19]. However, CAMHS is a very different context to adult services, and young people require different adaptations and considerations as part of psychological therapy.

RELATE-YP is a feasibility RCT that will evaluate the feasibility and acceptability of brief, 8-session CAT for young people (13–17 years) who self-harm. This age range has been chosen to coincide with when self-harm often first occurs [3]. brief CAT will be compared against treatment as usual (TAU). TAU has been selected as a comparator because no single approach is currently consistently implemented for young people who self-harm within UK services. Feasibility will be judged based on pre-specified progression criteria regarding recruitment rates, retention at follow-up, and missing data. Given finite healthcare resources, decision-makers require evidence demonstrating the cost-effectiveness of healthcare interventions. We will therefore also assess the feasibility of collecting the necessary data for a full economic evaluation of the intervention within a future trial. Acceptability will be investigated via a qualitative process analysis and therapy adherence rates. Adverse events (AEs) will be monitored as part of the study. Treatment effects on clinical outcome measures (e.g. self-harm behaviour and urges) will be estimated as this will help guide the design of a future definitive trial by informing key parameters (e.g. variance in outcome measures). This protocol has been drafted based on version II of the protocol (19/8/2025), in accordance with the updated Standard Protocol Items: Recommendations for Interventional Trials (SPIRIT) statement (see Supplement I; [26, 27]). The results of this feasibility trial will directly inform future clinical research into treatments for self-harm, determining if a definitive trial of brief CAT for self-harm is feasible, and if so, guiding the design and development of this deinfitive trial. A definitive trial would in turn contribute to clinical guidelines regarding effective treatments for self-harm in young people.

## Method

### Design, randomisation, and blinding

A single-blind feasibility RCT design will be undertaken whereby participants are randomly allocated on a 1:1 basis to either brief CAT plus TAU or TAU alone. Assessments will take place at baseline, 8-, 16-, and 20 weeks post-randomisation. Randomisation will take place after the baseline assessment and be conducted independently using SealedEnvelope.com, using a randomised block design (block sizes of 4 and 6 generated at random) that is stratified by site (NHS trust). Allocation concealment will be ensured by independent randomisation, with researchers involved in enrolling participants and assessment not having access to randomisation sequence. Members of the research team not blind to allocation will inform participants of their allocation. A flow chart of trial procedures is available in Fig. 1.

**Fig. 1 Fig1:**
[figure not shown]
Flow diagram of study procedures

Researchers completing assessments will be blind to treatment allocation. To help adherence to the study protocol, participants, families, and clinical teams will be briefed on the importance of blinding. Blinded researchers and trial therapists will not share offices. Blinding will be monitored throughout and blind breaks recorded. In the event of a break in blinding, an alternative researcher who is still blinded will undertake future assessments for that participant, where possible. The statistician will be blind to participant allocation status up until the creation of the statistical analysis plan (SAP) and its approval by the trial steering committee (TSC). Blinding may be broken where required to manage risk. Blinding of participants is not possible, as is typical in psychotherapy trials, because participants will know if they are receiving brief CAT. Whilst this increases the potential for performance bias, we will attempt to minimise bias overall by following best practice for trials of psychological therapies, such as using valid assessments, taking steps to reduce attrition, and carefully monitoring what other interventions participants access.

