### Safety monitoring and reporting

AEs and serious adverse events (SAE) will be monitored and recorded throughout the trial. SAEs will include events that result in death, are life-threatening, or result in hospitalisation. This will therefore include some but not all instances of self-harm. AEs related to self-harm behaviour and ideation, interpersonal conflict, and deterioration in mental health are expected. The research team will review all SAEs to determine the probability that the event is causally linked to study procedures or interventions based on available data (e.g. timing of event and participant report on antecedents). The TSC will have access to SAE reports and will provide independent monitoring of SAEs throughout the trial. The TSC will also monitor the overall number of AEs and SAEs occurring during the course of the trial. An imbalance in AEs and SAEs between trial arms is expected due to factors such as random variation and the increased participant contact for those in the brief CAT arm (i.e. AEs may be more readily identified due to the regular appointments). Any substantial imbalance will require a review.

Therapy may be discontinued in cases where this is required to maintain the safety of participants or others. Where SAEs are attributed to the trial procedures, this may be grounds to discontinue therapy or withdraw a participant from the trial altogether. A participant may be withdrawn if the research team are notified of a significant potential threat to the safety of a member of the research team or if a participant displays aggressive or abusive behaviour towards a member of the team. These decisions would be made in consultation with the participant’s clinical team, and the TSC, and would occur on a case-by-case basis. Where SAEs are attributed to the trial procedures, it may also be necessary to pause or stop the trial altogether, and such decisions will be made with the TSCs and the funder’s guidance.

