### Statistical analysis

As this is a feasibility study, we will report descriptive data on study ‘processes’ and ‘outcomes’. An intention-to-treat (ITT) protocol will be followed. Descriptive data concerning recruitment, retention, and attrition will be presented in a CONSORT flow chart [58]. Treatment engagement and attrition rates will be calculated with associated confidence intervals and reasons for leaving the trial or therapy early will be reported where available. Rates of missing data will be presented for outcome measures. Descriptive statistics will be presented for the overall sample and by group for all potential outcome measures. RELATE-YP is a feasibility study and inferential testing of treatment efficacy is therefore not the goal of the study. Nonetheless, we will estimate treatment effects and associated confidence intervals to inform planning for a future trial. These analyses will use an appropriate regression model, depending on the distribution of the outcome variable (e.g. linear regression for continuous outcomes, negative binomial regression for count outcomes). A detailed SAP will be drafted by the trial statistician and approved by the TSC prior to any analyses taking place. This will be available from the research team on request. No interim analyses are planned. Imputation may be used to generate total scores on scales where < 20% of items are missing but will not otherwise be used.

For the feasibility economic analysis, the extent of missing cost and outcomes data will be presented using descriptive statistics. The CHU9D will be used to derive quality-adjusted life years (QALYs), in line with National Institute for Health and Care Excellence (NICE) reference case [59]. The cost of delivering the intervention will be estimated based on the resources used as recorded by trial therapists. Published NHS and social care unit costs will be attached to these estimates of resource use. The identity and quantity of other health and social care resources used by participants will be captured and summarised. This information is required for a full economic evaluation and will be used to understand what services participants access as TAU to help define exemplar comparators for a future cost-effectiveness analysis. Data on what participants received as TAU will be presented in our final reporting and reviewed holistically to help inform the planning of a future definitive trial.

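### The statistician's blind ends at SAP approval rather than at database lock, so the protocol allows unblinding while outcomes are still being collected and cleaned

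*Protocol article*

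**What the plan says.** Three statements in the protocol article bear on this.

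- **When the blind ends.** Design, randomisation, and blinding: "The statistician will be blind to participant allocation status up until the creation of the statistical analysis plan (SAP) and its approval" by the TSC.
- **When the SAP must be approved.** Statistical analysis: "A detailed SAP will be drafted by the trial statistician and approved by the TSC prior to any analyses taking place". This is the only deadline. The article gives no calendar date and does not mention a database lock or data freeze. The same section adds: "No interim analyses are planned".
- **What is left open at protocol level.** Statistical analysis: "These analyses will use an appropriate regression model, depending on the distribution of the outcome variable", with linear regression for continuous outcomes and negative binomial regression for counts as examples. On missing items: "Imputation may be used to generate total scores on scales where < 20% of items are missing but will not otherwise be used".

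**The concern.** The blind is tied to a document and not to the state of the data. A SAP approved early in recruitment is usually good practice, yet under this rule it would unblind the statistician soonest. Allocation could then be known through the rest of follow-up and cleaning.

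A SAP sets rules, but someone applies them to real data. Self-harm counts from the SITBI are likely to be skewed. With 30 participants planned per arm, the handling of a few extreme or doubtful values can move a negative binomial rate ratio. Item-level imputation is worded as optional. If such decisions are taken with allocation known, a reader cannot exclude that they were influenced by it.

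The estimates will be used. The Introduction says treatment effects and outcome variance will guide the design of the definitive trial. Primary outcomes says the suitability of the two candidate primary outcomes will rest partly on statistical considerations.

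**Working it through.** The protocol gives no figure to reproduce here. The check has two parts: whether the text permits early unblinding, and how much data could be outstanding if it happened.

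**1. Reading the passages together.** The blind ends at SAP approval. Approval must precede any analysis. No interim analyses are planned, so the first analysis would presumably follow the end of data collection. Approval at any time from the start of recruitment up to that first analysis satisfies the text. Early unblinding is therefore permitted, but it is not stated as the plan.

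**2. Share of visits outstanding at approval.**

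Inputs from the protocol:
- Recruitment of 60 participants over 12 months, taken as 52 weeks (Primary outcomes, Table 1).
- Follow-up at 8, 16 and 20 weeks after randomisation (Design, randomisation, and blinding).
- The 16-week visit is named as the potential primary outcome timepoint (Table 1).

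Assumptions: even accrual, full recruitment, no attrition. The week of approval, t, is not stated, so it is varied.

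Formula for a visit at week w: outstanding share = 1 − (t − w)/52, held between 0 and 1.

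For the 16-week visit:
- t = 16 or earlier: 100%
- t = 26 (month 6): 1 − 10/52 = 81%, about 48 of 60 visits
- t = 39 (month 9): 1 − 23/52 = 56%
- t = 42: 1 − 26/52 = 50%
- t = 52 (month 12): 1 − 36/52 = 31%, about 18 of 60 visits
- t = 68 or later: 0%

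For all three post-baseline visits, averaging the three shares:
- t = 26: (65.4 + 80.8 + 88.5)/3 = 78%
- t = 39: (40.4 + 55.8 + 63.5)/3 = 53%
- t = 52: (15.4 + 30.8 + 38.5)/3 = 28%
- t = 72 (last 20-week visit): 0%

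The share for all visits falls to 50% at (8 + 16 + 20)/3 + 26 = 40.7 weeks. More than half of outcomes would therefore be outstanding only if approval came before about week 41 (all visits) or week 42 (16-week visit).

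These percentages measure how much data collection could take place with an unblinded statistician. They do not measure bias, and no shift in any estimate has been calculated.

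**The case against.** **The SAP is written under blind.** The statistician drafts it and the TSC approves it before allocation is known. Model family and item-imputation rules are what a SAP normally fixes, and this SAP is not shown. The regression choice is illustrated by outcome type, which can be settled in advance; the text does not say it waits for the observed data. This stands, and it narrows the concern to the application of rules and to whatever the SAP leaves open. It does not remove it, because the blind ends at the approval of that SAP, before its rules are necessarily applied to complete data.

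**The timing is unknown.** Approval after last follow-up fits the text as well as approval at month 6. A reader might infer that the statistician will be unblinded while most outcomes are still being collected. The documents do not support that as a fact; it holds only for approval before about week 41 or 42.

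**Other safeguards exist.** Researchers completing assessments are blinded independently of the statistician. Data management provides for pre-specified admissible values and 10% parallel data entry. These stand and limit the harm.

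**The TSC.** A reader might also infer that late approval is compromised because the TSC would already have seen self-harm events by arm. Safety monitoring and reporting does state "Any substantial imbalance will require a review", but it names no reviewer and describes the TSC as monitoring overall numbers of events. Trial management gives the data-monitoring role to a subgroup of the TSC. Nothing says that the approving committee sees adverse events by arm before it approves the SAP, so that inference is not established.

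**Conclusion.** The point holds as a low-severity improvement. The protocol states a rule for ending the statistician's blind, and that rule permits unblinding before follow-up and cleaning are complete. How far this would happen depends on an approval date that is not given. Under even accrual with no attrition, the outstanding share of 16-week visits runs from 100% to 0%, with 81% at month 6 and 31% at month 12 as examples.

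The consequence is modest. The primary outcomes are feasibility criteria that the Sample size section says are not evaluated separately by arm. Efficacy testing is not a goal, and no sample size or precision figure changes. What is exposed is the credibility of the between-arm estimates carried forward to plan the definitive trial.

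**What to change.** In Design, randomisation, and blinding, replace the sentence on the statistician with wording such as:

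*The statistician will remain blind to allocation until the SAP has been approved by the TSC and the database has been locked. Any data-handling decisions that the SAP leaves open will be made before lock on data pooled over arms.*

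The cost is minimal. No interim analysis is planned, so the article gives no analytic reason for the statistician to need allocation before lock. Any by-arm tabulation needed earlier must be prepared by someone already unblinded, and the same section says that such team members exist. Therapy attendance and session forms arise only in the brief CAT arm, so they should be withheld from the statistician until lock.

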### Trial setting and participants

The trial will take place across three large and demographically diverse NHS Trusts in the North of England. Participants will be young people with experiences of self-harm who will be recruited through CAMHS and associated services (e.g. mental health in schools’ teams, other outpatient psychology services for young people).

Participants will be required to meet the following inclusion criteria:Aged 13–17 years.Engaged in self-harm, following the NICE definition [1], two or more times in their lifetime, with at least one episode in the past year. This will be confirmed via the Self-Injurious Thoughts and Behaviours Interview Short Form (SITBI; [28]).Can be safely seen in an outpatient clinical context in which treatment is being provided as judged by their clinical team or referrer.

Exclusion criteria will be as follows:Moderate-to-severe intellectual disability (IQ: < 70) as judged by a young person’s clinical team.Organic cerebral disease/injury affecting receptive and expressive language comprehension as judged by a young person’s clinical team.Currently an inpatient.Currently experiencing an active episode of mania or psychosis, assessed with the Mini International Neuropsychiatric Interview for Children and Adolescents (MINI-KID; [29]).Judged at imminent risk of harm to themselves, operationalised as presence of intent or planning to end their lives within the near future (e.g. next 2 weeks). In such cases, individuals could still participate once the level of risk has declined.Currently receiving another active one-to-one psychological therapy. This would include structured psychological therapies such as CBT or DBT. Other forms of support, like a support group or skills group, seeing a clinician for informal support or medication advice, or engaging with self-help materials, will not exclude people.

